### Participants

The clusters are nursing homes. There will be eight private for-profit NHs in Hong Kong. They will be those that have been classified as category A2 homes in the Enhanced Bought Place Scheme (EBPS) and eager to improve the pressure ulcer prevention care that they currently offer, have a capacity of around 130–140 beds, and have no PU prevention protocol in place. We believe that EBPS-A2 homes will represent the target population of for-profit private NHs in Hong Kong because they hire few or no professional nurses but are considered more motivated to improve the quality of the care that they provide than non-EBPS homes, and would perhaps therefore be more likely than the latter to comply with the protocol. The study sample will be the residents and care staff from the eight private for-profit NHs in Hong Kong. The residents will be those aged 60 or above and the care staff will include personal care workers (PCWs) and health workers (HWs) who provide direct care to residents.

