### Randomization

Randomization will be carried out after the written informed consent of all individual residents to participate this study has been obtained and the recruitment of residents from the eight nursing homes has been completed. The PI will assign each nursing home that has agreed to join the study a number of from one to eight. A trained RA using the random number generator will randomly assign four numbers to the experimental group and the remaining four numbers to the control group. In accordance with the randomized numbers, the PI will assign the eight nursing homes to the experimental or control groups.

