### Statistical analysis

IBM SPSS Statistics 22 will be used to analyse the data. An intention-to-treat analysis will be adopted. Descriptive statistics such as mean or percentage will be used to summarize PU prevention knowledge and skills, and the prevalence and incidence of PUs. A chi-square test will be performed to compare the PU prevalence and PU incidence of residents between the two groups. An independent t-test will be adopted to compare the knowledge and skills of care staff between the two groups. Generalized estimating equation (GEE) will be used to compare the two groups in terms of their performance in the knowledge and skills tests, as well as in PU status over time, and to examine the groups by the time interaction effect, adjusting for the cluster effect and possible confounders. Significance will be set at a P value of < =0.05.

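### The only cluster-adjusted analysis is a GEE on eight homes with no small-sample inference named; in its ordinary form it would reject a true null about 14 % of the time rather than 5 %

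*Protocol article*

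**What the plan says.** The Participants section sets the number of clusters: "There will be eight private for-profit NHs in Hong Kong". Under Randomization, a research assistant "will randomly assign four numbers to the experimental group and the remaining four numbers to the control group".

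The Statistical analysis section names three inferential methods:

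- Resident outcomes: "A chi-square test will be performed to compare the PU prevalence and PU incidence of residents between the two groups".
- Staff outcomes: "An independent t-test will be adopted to compare the knowledge and skills of care staff between the two groups".
- A GEE for staff scores and pressure ulcer status over time, which will also "examine the groups by the time interaction effect, adjusting for the cluster effect and possible confounders".

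Only the GEE is described as allowing for clustering. One threshold covers everything: "Significance will be set at a P value of < =0.05". The section does not give the GEE's subject unit, working correlation, variance estimator, test statistic or reference distribution. It mentions no small-sample correction, permutation test or analysis of home-level summaries.

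**The concern.** The robust (sandwich) variance of a GEE is justified when there are many independent clusters. With four per arm, two things go wrong in the same direction. The uncorrected sandwich variance is too small on average, and the Wald statistic is compared with a normal distribution although the variance rests on only 8 − 2 = 6 between-home degrees of freedom. Both push the true error rate above the stated 5 %.

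Pressure ulcer incidence and prevalence are the primary outcomes, and the GEE is the analysis that readers would trust for them because it is the one that recognizes the cluster design. The Discussion foresees recommending the programme to nursing homes in Hong Kong or elsewhere, so a false positive would have consequences.

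**Working it through.** **Inputs.**
- Homes per arm k = 4 (Participants; Randomization).
- Nominal level 0.05 (Statistical analysis). Sidedness is not stated; two-sided is assumed.
- Event rates 9.5 % and 6 %, ICC 0.001, and 784 residents after the clustering allowance (Sample size), so 784/8 = 98 per home.
- ICCs other than 0.001 are assumptions, used to show a range.

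**The plan's own figure.** The only figure to compare with is the nominal 0.05. The article reports no error rate for the GEE.

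**Exact size, ordinary GEE.** Take equal homes with normally distributed home means. The uncorrected sandwich variance is (k − 1)/k = 3/4 of the unbiased between-home variance. The Wald test therefore rejects when a t statistic on 6 df exceeds 1.96 × √0.75 = 1.697:

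2 × P(t₆ > 1.697) = 0.1405.

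**Repairing only one half.**
- Corrected variance, normal reference: 2 × P(t₆ > 1.96) = 0.098.
- Uncorrected variance, t₆ reference: 2 × P(t₆ > 2.447 × √0.75) = 2 × P(t₆ > 2.119) = 0.078.
- Both repaired: 2 × P(t₆ > 2.447) = 0.050.

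**Simulation under the null.** Beta-binomial data, 4 + 4 homes, 98 residents each, event probability 0.095, 200,000 runs per setting. The GEE has the home as cluster and compares two groups at one time.

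| ICC | Ordinary robust GEE, z | Variance × 4/3, t₆ | Chi-square, no clustering |
|---|---|---|---|
| 0 | 13.8 % | 4.8 % | 5.0 % |
| 0.001 | 13.8 % | 4.8 % | 6.1 % |
| 0.01 | 14.0 % | 4.9 % | 16.1 % |
| 0.02 | 14.5 % | 5.1 % | 25.5 % |
| 0.05 | 15.5 % | 5.6 % | 41.7 % |

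- With 136 residents per home or an event probability of 0.0775, the GEE column stays between 13.7 % and 16.2 %.
- With home sizes varying by a CV of 0.2, it is 14.2 % (ICC 0.001) and 14.5 % (ICC 0.01).
- Fitting 1,500 exchangeable logistic GEEs with robust variance (ICC 0.01) gave 13.3 %, Monte Carlo SE 0.9 points.
- Continuous staff scores gave 14.0 to 14.1 %.
- A home-level t-test on 6 df gave between 4.5 % and 5.2 %.

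The GEE figure hardly moves with the ICC, event rate or home size because it comes from the number of homes. More residents per home would not cure it.

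**If the resident is the GEE subject and home is ignored.** The variance is understated by the design effect 1 + (98 − 1) × ICC.
- ICC 0.001: design effect 1.097; 2 × P(Z > 1.96/√1.097) = 2 × P(Z > 1.871) ≈ 6.1 %.
- ICC 0.01: design effect 1.97; 2 × P(Z > 1.96/√1.97) = 2 × P(Z > 1.396) ≈ 16.3 %.

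These agree with the simulated chi-square column, which ignores home in the same way.

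**The case against.** The strongest reply is that the article never says robust, uncorrected or Wald. A GEE with a small-sample correction and a t reference would still fit its sentence, and such detail often sits in an analysis plan that is not shown here. This stands in part: 14 % is the size of the method in its ordinary form, not of a procedure that the text fully fixes. What does not fall away is that the article chooses a method and a threshold for an eight-cluster design, and running that method as it is ordinarily run does not give the threshold.

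Three further limits stand.

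- **Subject unit.** The GEE handles repeated measures, so the resident could be its subject. The error then depends on the ICC and, at the plan's own 0.001, is only about 6 %. That reading sits poorly with an analysis said to allow for the cluster effect, but the text does not exclude it.
- **What was simulated.** The calculation is a two-group comparison at one time, without covariates. This matches the first hypothesis, a group difference at the end of implementation, but not the interaction test.
- **Confounders.** A reader might infer that home-level confounders will consume the remaining degrees of freedom. The article names no confounders at any level, so this cannot be charged against it.

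A reader might also infer that every named test badly exceeds 5 %. The documents do not support that: the chi-square is at about 6 % under the planning ICC, and its larger inflation needs an ICC that the plan does not assume.

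**Conclusion.** The concern holds conditionally. With the home as the GEE cluster, an uncorrected robust variance and a Wald test against the normal or chi-square distribution, a two-group comparison at a nominal 5 % has a true size of about 14 % (14 to 16 % for ICCs from 0 to 0.05), nearly three times the stated level. The size of the group-by-time test with covariates was not computed and could differ from 14 %, but it faces the same limit of about 6 between-home degrees of freedom. It would be too strong to say that the planned test has a 14 % error rate without qualification, because the article does not state these three conditions. The matter should still be settled before any comparison by arm, since a choice of small-sample method made after seeing results would be open to challenge.

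**What to change.** State that the nursing home is the cluster, and name one small-sample procedure for the group comparison. Either of these is sound:

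1. A home-level (two-stage) t-test on 6 df, or an ANCOVA on home summaries with one covariate on 5 df.
2. A GEE with a Kauermann-Carroll or Mancl-DeRouen variance correction and a t reference on 6 df. Both the correction and the t reference are needed, since either alone leaves the size near 8 to 10 %.

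An exact permutation test over the C(8,4) = 70 allocations can support either one. Its smallest two-sided P is 2/70 = 0.029, so it can reach significance at 0.05. If any home-level covariate is used, limit it to one.

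The cost is a change of wording. The home-level test runs in any package; if the GEE route is kept, confirm that the named software (SPSS 22) offers the correction.

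The downside is lower nominal power: at 9.5 % against 6 %, ICC 0.001 and 98 residents per home, rejection falls from an inflated 54 % to about 32 %. Much of that shortfall has another source. Those rates need about 915 residents per group before any allowance for clustering (two-sided 0.05, 80 % power), against the 355 stated under Sample size. That is a separate error and should be corrected on its own account.

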## Discussion

PU prevention programmes require attention not only to content but also to implementation and sustainability strategies [22]. According to the researcher’s experience from previous studies on preventing pressure ulcers, there are several potential challenges to the implementation of this protocol. First, insufficient PU prevention materials in for-profit private nursing homes, including pressure-relieving mattresses, seating cushions, and heel protectors, will be a barrier to the implementation of the protocol [26]. Second, the inadequate manpower and high workload of care staff in for-profit private nursing homes will likely affect staff compliance with the protocol. Finally, there is the high turnover rate of nursing home care staff, which will affect the quality of the care that is delivered, including the quality of the PU prevention care. The new care staff will need to be trained in the knowledge and skills in PU prevention care required for the implementation of the protocol. The research team has considered some strategies for dealing with these challenges that they will likely encounter in the implementation of the protocol. This research project will potentially confirm the effect of the programme. The evidence-based pressure ulcer prevention programme will be recommended to for-profit private nursing homes in Hong Kong or elsewhere, where the majority of care staff members are not professionals and have received less training than nurses, and where no PU prevention protocol has been put in place.

## Abbreviations

GEE: Generalized estimating equation
HWs: Health workers
MBS: Modified braden scale
PCWs: Personal care workers
PI: Principal investigator
PU: Pressure ulcer
RA: Research assistant
RCHs: Residential care homes
NH: Nursing home
